### 14.2 Participant insurance

The participants will be insured in accordance with existing legislation of their respective country.

### 14.3 Publication plan

The trial will be registered on ClinicalTrials.gov prior to the randomisation of the first participant. Attempts will be sought to publish all results, positive, neutral, as well as negative, in a peer-reviewed international journals. Authorship will be determined according to the International Committee of Medical Journal Editors. Attempts will be made to publish a list of all investigators with their contributions in all publications.

## 15. Appendices

### 15.1 Appendix A: Treatment guidelines and justifications

#### SafeBoosC Clinical Guidelines

##### Assessment of cerebral oxygen saturation

Regional cerebral tissue oxygen saturation (rStO2) is a composite measure of tissue oxygen saturation across arterial, capillary and venous beds and reflects a balance between cerebral oxygen delivery (CDO2) and cerebral metabolic rate (CMRO2). In preterm infants, the CMRO2 is unlikely to vary much and a change in rStO2 largely reflects changes in CDO2. The factors which influence CDO2 are arterial oxygen saturation (SaO2), haemoglobin concentration ([Hb]), and cerebral blood flow (CBF).

##### Establishment of monitoring of cerebral oxygenation

As soon as possible and within 3 hours of age

##### Period of monitoring of cerebral oxygenation

Until 72 hours after birth

##### Instruction

Document the intervention chosen and any changes in rStO2 following intervention.

##### Recommendation for clinical interventions

The rStO2 target normal range is 55% to 85%. If the rStO2 is out of normal range and there is no reason to believe that it will normalise without intervention, consider one of the interventions (identified in '•') listed below and reassess 30 to 60 minutes after the intervention. Generally, only one intervention should be chosen at a time. All the interventions proposed here are commonly used in this patient group. After each intervention, the level of evidence for each intervention (I-III) and recommendation (A-E) are given (defined in table 1 and 2). For further explanation, see below.

##### rStO2 < 55%

Aim of intervention: A low rStO2 reflects a low CDO2. The interventions should be directed to increasing SaO2, [Hb], and/or CBF.

##### Assess cardiovascular status:

Blood pressure below the normal range or low, even in the normal range, consider:

- Vasopressor-inotropes (I/B) (54,55)
- Fluid bolus (normal saline) (I/C) (56,57)
- Decrease mean airway pressure (III/B) (58-61)

Poor systemic circulation, consider if:

Echocardiography shows low cardiac output and/or low SVC flow

- Inotropes (I/B) (57,62-66)
- Fluid bolus (normal saline) (I/C) (56,57)
- Decrease mean airway pressure (III/B) (58-61)
- Reduce vasopressor (III/ B) (67)

Echocardiography not available but has at least 2 of the following signs:

Lactate > 3.5 mmol/l

CRT > 3 seconds

Urine output < 1 ml/kg/hour

consider:

- Inotropes (I/B) (57,62-66)
- Fluid bolus (normal saline) (I/C) (56,57)
- Decrease mean airway pressure (III/B) ) (58-61)
- Reduce vasopressor (III/B) (67)

Patent ductus arteriosus, consider:

- Medical treatment (II-2/B) (44,59,60,68)

#### Assess oxygen transport:

Haemoglobin below the normal range or low, even in the normal range, consider:

Red blood cell transfusion (I/B) (69-72)

#### Assess respiratory status:

SaO2 below the normal range or low, even in normal range, consider:

- Increase FiO2 (II-1/A) (73) (ATTENTION: be careful not to exceed the upper target threshold of SpO2)
- Increase mean airway pressure (III/B) (58,74,75)

PCO2 below the normal rangen or low, even in normal range, consider:

- Decrease minute ventilation (II/A) (69,76-78)

#### **rStO2 > 85%**

Aim of intervention: A high rStO2 reflects impaired oxygen utilisation and/or disturbed cerebral autoregulation (hyperaemia) and interventions should be directed at identifying and treating the underlying cause.

#### Assess respiratory status:

SaO2 above the normal range or high, even in normal range, consider:

Decrease FiO2 (II-2/A) (79-83)

Decrease mean airway pressure (III/B) (74,75)

PCO2 above the normal range or high,, even in normal range, consider:

Increase minute ventilation (II/A) (69,76-78)

#### Assess blood glucose level:

Blood glucose < 2.5 mmol/l, consider to:

Increase glucose intake (II/A) (84,85)

#### **Level of evidence and recommendation of intervention**

The level of evidence (Table 1) and recommendation for a given intervention (in brackets and Table 2)) were graded according to the U.S. Preventive Services Task Force system (86)

Table 1: Hierarchy of research design and level of evidence

| Level of evidence | Type of study                                                                                                                                                                                                                                         |
|-------------------|-------------------------------------------------------------------------------------------------------------------------------------------------------------------------------------------------------------------------------------------------------|
| I                 | Evidence obtained from at least one properly randomized controlled trial                                                                                                                                                                              |
| II-1              | Evidence obtained from well-designed controlled trials without randomization                                                                                                                                                                          |
| II-2              | Evidence obtained from well-designed cohort or case-control analytic studies, preferably from more than one centre or research group                                                                                                                  |
| II-3              | Evidence obtained from multiple time series with or without intervention. Dramatic results in uncontrolled experiments (such as the results of the introduction of penicillin treatment in the 1940s) could also be regarded as this type of evidence |
| III               | Opinions of respected authorities, based on clinical experience,                                                                                                                                                                                      |

|  |                                                                       |
|--|-----------------------------------------------------------------------|
|  | descriptive studies and case reports, or reports of expert committees |
|--|-----------------------------------------------------------------------|

Table 2: Recommendation grid

| Quality of evidence              | Net benefit                                                                                                                                                                                                                                                                                                                                                                                                                                                                                                                                                                                                                                                                                                                                                                                                                                                                                                                                               |          |       |               |
|----------------------------------|-----------------------------------------------------------------------------------------------------------------------------------------------------------------------------------------------------------------------------------------------------------------------------------------------------------------------------------------------------------------------------------------------------------------------------------------------------------------------------------------------------------------------------------------------------------------------------------------------------------------------------------------------------------------------------------------------------------------------------------------------------------------------------------------------------------------------------------------------------------------------------------------------------------------------------------------------------------|----------|-------|---------------|
|                                  | substantial                                                                                                                                                                                                                                                                                                                                                                                                                                                                                                                                                                                                                                                                                                                                                                                                                                                                                                                                               | moderate | small | zero/negative |
| Good                             | A                                                                                                                                                                                                                                                                                                                                                                                                                                                                                                                                                                                                                                                                                                                                                                                                                                                                                                                                                         | B        | C     | D             |
| Fair                             | B                                                                                                                                                                                                                                                                                                                                                                                                                                                                                                                                                                                                                                                                                                                                                                                                                                                                                                                                                         | B        | C     | D             |
| Poor                             | E                                                                                                                                                                                                                                                                                                                                                                                                                                                                                                                                                                                                                                                                                                                                                                                                                                                                                                                                                         | E        | E     | E             |
| Standard recommendation language | 
A= Strongly recommended (good evidence that the intervention improves important health outcomes and benefits substantially outweigh harms).
 
B= Recommended (at least fair evidence that the intervention improves important health outcomes and benefits substantially outweigh harms).
 
C= No recommendation for or against routine provision of the intervention (fair evidence that the service can improve health outcomes but the balance of the benefits and harms is too close to justify a general recommendation).
 
D= Recommends against routinely providing the intervention (at least fair evidence that the service is ineffective or that harms outweigh benefits).
 
E= Insufficient to recommend for or against routinely providing the intervention (evidence that the intervention is effective is lacking, of poor quality, or conflicting and the balance of benefits and harms cannot be determined).
 |          |       |               |

**Abbreviations**

|       |                                            |
|-------|--------------------------------------------|
| SVC   | Superior vena cava                         |
| CRT   | Capillary refill time                      |
| FiO2  | Fraction of inspired oxygen                |
| rStO2 | Regional cerebral tissue oxygen saturation |
| SaO2  | Saturation of Oxygen (arterial blood)      |
| PCO2  | Partial Pressure of Carbon Dioxide         |
| CDO2  | Cerebral oxygen delivery                   |
| CMRO2 | Cerebral metabolic rate                    |
| [Hb]  | Haemoglobin concentration                  |
| CBF   | Cerebral blood flow                        |

## 15.2 Appendix B: Procedure for assessment of chemical biomarkers

### OUTCOME MEASURES

Outcome measure 1: S100 $\beta$

Outcome measure 2: BFABP

Outcome measure 3: Neuroketal

### MEDIUM

#### Blood

If a central blood catheter is in place up to one ml of blood will be collected in **heparin**.

Commercially available tubes containing lithium or sodium heparin are available to collect 2 ml of blood. These tubes can be used without vacuum and filled with 1 ml from a syringe. The higher final heparin concentration is no problem. Tubes with a gel to aid separation of plasma may be used, and must be used if less than 1 ml is drawn (if using gel separator tubes, follow the manufacturers instructions leaflet) .

**EDTA or citrate plasma cannot be used for measurement of S100 $\beta$ .** Blood must be kept cold after collection on ice or in the fridge at 4°C  $\pm$ 2°C until it is centrifuged (1200xg for 12 minutes in a normal centrifuge or 13000 rpm in a microcentrifuge) to obtain platelet poor plasma. As much as possible plasma is then collected, transferred to small screw-cap tubes and stored frozen (-20°C  $\pm$ 4°C for a maximum of one week, thereafter at -80°C  $\pm$ 10°C for prolonged storage).

#### Urine

If possible, 1 ml of urine shall be collected and stored frozen (-20°C  $\pm$ 4°C for a maximum of one week, thereafter at -80°C  $\pm$ 10°C for prolonged storage) without further treatment.

### TIME OF COLLECTION

Blood: (can be +/-1 hours of specified time points):

- 6 hours after birth, and
- 64 hours after birth

Urine (if possible) - (can be +/-1 hours of specified time points):

- 6 hours after birth, and
- 64 hours after birth.

### STORING

Samples should be labeled with two country letters, identification (randomisation number), Plasma or Urine, time points .. Example: DK 5 P 2 = Rigshospitalet participant 5, plasma collected after 64 hrs. The principal investigator shall keep record of the participant identity linked to the participant number. All samples should be stored at the site until last participants samples has been collected and recorded.

### SHIPPING:

When last participant has been enrolled, samples should, immediately hereafter, be shipped in batches on dry ice, using DHL as a courier. Shipping will always be Monday or Tuesday.

To the following address:

Haemoscan B.V.  
[name]  
[name], The Netherlands  
Att: [name]

[contact]  
Fax nr [name]

Material transfer agreements between Haemoscan and the sites will be issued by each institutions legal department.

**METHODS OF ASSESSMENT**

All assessments are conducted without knowledge of allocation group (experimental or control).

**S100 $\beta$** 

The S100 $\beta$  serum-concentration will be assessed by ELISA. It can be detected in heparin plasma, heparin serum or urine in 50  $\mu$ l samples.

**BFABP**

Brain fatty acid binding protein (BFABP) is determined by means of ELISA with BFABP specific monoclonal capture antibodies and polyclonal detection antibody in plasma/serum as well as urine. 100  $\mu$ l is needed for a BFABP ELISA, due to its low concentrations.

**Neuroketal**

Determination of neuroketal is performed by competitive enzyme immunoassay in 100  $\mu$ l of plasma/serum or urine.

**Abbreviations**

|                               |                                                            |
|-------------------------------|------------------------------------------------------------|
| S100<math>\beta</math> | Acidic calcium binding protein found in the nervous system |
| BFABP                  | Brain fatty acid binding protein                           |
| ELISA                  | Enzyme linked immunosorbent assay                          |
| ml                     | Millilitre                                                 |

SafeBoosC phase II

## 15.3 Appendix C: Procedures for assessment of aEEG/EEG

### OUTCOME MEASURES

Outcome measure 1: Interburst interval (IBI)  
Outcome measure 2: Power in delta band  
Outcome measure 3: Power in theta band  
Outcome measure 4: Power in alpha band  
Outcome measure 5: Power in beta band  
Outcome measure 6: Background pattern  
Outcome measure 7: Sleep wake cycling  
Outcome measure 8: Seizures

### MEDIUM

Raw EEG-data

### TIME OF COLLECTION

Single-channel EEG is applied for at least 120 minutes at 56-72 hours after birth. This should be at least 3 hours after administration of bolus morphine, if possible. Hydrogel electrodes or needle electrodes may be used. P3 and P4 positions according to the international 10–20 system; a frontal reference electrode is also applied.

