| Investigator's
assessment and
medical records                                                                                                                                                                                                                   | 
 
• Serious adverse reactions
 
• Non-serious adverse reactions
 
                                                                                                             | 
 
• During the intervention until 72 hours after birth
 
                                                                                                                                                                                                                       | Not centralised                                                                               |
| cUS
(Appendix E)                                                                                                                                                                                                                                                   | 
 
• IVH grade (Papille)
 
• Cerebellar haemorrhage
 
• cPVL
 
• Cerebral atrophy
 
• Post-haemorrhagic hydrocephalus
 
                                   | During the intervention and follow-up period, according to these assessment points: 
 
• At 1 day after birth
 
• At 4 days after birth
 
• At 7 days after birth
 
• At 14 days after birth
 
• At 35 days after birth
 
• At 40-44 weeks
 
 | Department of Neonatology,
Wilhelmina Children's hospital, UMC Utrecht,
The Netherlands |

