| * If assessment is not possible at the specified time, the assessment shall still be conducted, and the time will appear in the eCRF and the deviations from the CIP can be assessed.
# Central assessment is conducted by a blinded outcome assessment committee. |                                                                                                                                                                                                                                    |                                                                                                                                                                                                                                                                                                                              |                                                                                               |

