## 8. Assessment of safety

### 8.1 Adverse events and reactions

#### 8.1.1 Definitions

**Adverse events (AE):** any undesirable event occurring to a participant during a clinical trial, whether or not considered related to the trial intervention.

**Serious adverse event (SAE):** any adverse event that results in death, is life-threatening, requires prolongation of existing hospitalisation, result in persistent or significant disability or incapacity, or requires intervention to prevent permanent impairment or damage.

**Adverse reactions (AR) / Adverse device effects (ADE):** all untoward and unintended responses related to the interventions of application of the treatment guideline and/or cerebral oximeter.

**Expected adverse reactions (EAR) / Expected adverse device effect (EADE):** adverse reactions, we expect to be related to the interventions cerebral NIRS oximeter and/or the application of the treatment guideline are:

- Local skin reactions (rashes, burns, etc.).
- Reactions related to the manipulation of the patient during positing and re-positing of the cerebral NIRS oximeter sensors.
  - Accidental displacements of the endotracheal tube or extubation.
  - Accidental displacement of venous or arterial catheters,
  - Severe hypoxia or bradycardia otherwise unexplained.
- Other expected adverse reactions encompass reactions to any interventions directed at correcting an out-of-range oximeter reading by improving respiratory status, cardiovascular status, oxygen transport, and blood glucose level (see appendix A).

**Unexpected adverse reactions (UAR):** all untoward and unintended responses, that not is an expected reaction, related to the interventions cerebral oximeter and/or application of the treatment guideline.

**Serious adverse reactions (SAR):** any adverse reaction that results in death, is life-threatening, requires prolongation of existing hospitalisation, results in persistent or significant disability or incapacity, or requires intervention to prevent permanent impairment or damage. This definition includes

**Serious adverse device effect (SADE):** adverse device effect that has resulted in any of the consequences characteristic of a SAE, or are due to

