#### 8.1.4 Justification for recording and reporting periodicity and modality

The preterm patient population is a very seriously ill group. Most adverse events may be of a serious nature with or without the SafeBoosC trial intervention, and both intervention groups are expected to have a very high proportion of serious adverse events. It is therefore not possible, nor meaningful to record and report all adverse events. The following will be recorded and reported (for overview refer to table 4):

Adverse reactions (i.e. both expected (EAR) and unexpected (UAR) with a 'certain' or 'probable/likely' relation (see table 3) to the interventions will be recorded together with an assessment and reported with the trial results, The final report clinical investigation report to the competent authorities will summarize the ARs, including a discussion of causal relationship with investigational device, severity, and treatment needed.

Serious adverse events (SAE) to be recorded are: mortality; the mortality is high and will thus be analysed and reported as a secondary outcome measure and thus will not be reported to the authorities, and neonatal morbidities; these are believed to be the most important predictors for later development and health, and are recorded and reported as an outcome measure (necrotising enterocolitis stage 2-3, oxygen requirement, and

retinopathy of prematurity stage 3+ and above, as well as severe intraventricular haemorrhage and periventricular leucomalacia) thus not reported to the competent authorities.

Serious adverse reactions (i.e., both expected (ESAR) and unexpected (SUSAR) related to the cerebral oximeter and/or the treatment guideline will be recorded and analysed as a secondary outcome measure, but only SUSARs will subject to expedited reporting. Due to the nature of the population and the intervention, the near-incidents (**SAE-NI**) will be recorded, but not reported to the authorities.

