### TIME OF COLLECTION

At 40-44 weeks of gestational age.

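### Non-fatal harm from the trial's own EEG, research blood sampling and term MRI falls outside every adverse-event category the protocol records, unless it is a listed morbidity

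*Protocol*

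**What the plan says.** **Procedures done for the trial.** Appendix C sets the EEG without conditions: "Single-channel EEG is applied for at least 120 minutes at 56-72 hours after birth". It adds "Hydrogel electrodes or needle electrodes may be used", so needles are an option and not a requirement. Appendix B and section 7.3 plan blood samples at 6 and 64 hours, subject to a condition: "If a central blood catheter is in place up to one ml of blood will be collected". Appendix D times the MRI: "At 40-44 weeks of gestational age". The MRI has separate parental information and consent (Appendices H and I). The footnote to Table 1 keeps late assessments alive: "If assessment is not possible at the specified time, the assessment shall still be conducted".

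**What counts as harm.** Section 8.1.1 defines adverse reactions as "all untoward and unintended responses related to the interventions of application of the treatment guideline and/or cerebral oximeter". The unexpected, serious and suspected unexpected serious categories all build on that definition. Table 4 has a dash under Recorded for adverse events and serious adverse events in general. Section 8.1.4 gives the reason: this is a very ill population, and "It is therefore not possible, nor meaningful to record and report all adverse events". Deaths and a fixed list of neonatal morbidities are recorded whatever their cause.

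**When and to whom.** Table 1 gives the reaction window as "During the intervention until 72 hours after birth". Table 2 has its last mark for serious adverse reactions at the 7-day visit. Section 8.1.5 sends serious reactions to the sponsor within 24 hours. Section 8.3 asks the safety committee to monitor suspected unexpected serious reactions related to the oximeter or the guideline.

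**The concern.** Harm capture rests on attribution to two named interventions, but the trial also performs procedures on these infants that are neither. A harm that belongs to such a procedure meets the general definition of an adverse event, which the protocol does not record, and cannot meet the definition of a reaction, which it does.

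The protocol itself treats handling as a hazard. Section 8.1.1 lists tube displacement or extubation, catheter displacement, and otherwise unexplained severe hypoxia or bradycardia as expected reactions when the oximeter sensor is positioned or moved. The same event while EEG electrodes are applied has no category. Nor does a catheter displaced during research sampling.

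At stake is the completeness of the safety record. If the final report mentions no procedure-related harm, a reader cannot tell whether none occurred or none was collected. A serious event would also bypass the people charged with reacting to it.

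**Working it through.** The protocol gives no figure to reproduce. The check sets each procedure against the recording rules.

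| Procedure | Who has it | Within a recording window? | Within the reaction definition (8.1.1)? | Result |
|---|---|---|---|---|
| EEG, 56-72 h (Appendix C) | Every infant; needles optional | Yes | No | Not captured |
| Blood, 6 h and 64 h (7.3, Appendix B) | Infants with a central catheter in place | Yes | No | Not captured |
| MRI, 40-44 weeks (Appendix D) | Infants with MRI consent who reach term | No: after 72 h (Table 1) and 7 days (Table 2) | No | Not captured |

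In all three rows the exception is a death or a listed morbidity. That is recorded, but as an outcome and without attribution to a procedure.

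**Do other sections close the gap?**
- Section 8.1.3 opens by saying that adverse events are recorded and reported under the device directives, but then replaces this with the modality of 8.1.4. Table 4 shows the result.
- Section 8.3 repeats the oximeter-or-guideline restriction, so the committee has no wider view.
- Section 9.2 covers risks of the device and of the guideline only. Among the sampling procedures, only urine collection has a risk statement (7.3).
- Section 4.4 records the reason for a withdrawal. A harm that led to withdrawal would leave a trace there, but not as a safety event.

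**Size.** Scheduled procedures per infant: 1 EEG + 2 blood samples + 1 MRI = 4. With the planned 166 infants, 4 x 166 = 664. This is a ceiling. It falls for infants without a central catheter, without MRI consent, or who die. As an illustration, if the roughly 20% mortality in the Summary applied before term, at most 166 x 0.80 = about 133 infants could have the MRI.

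**What recording would add.** With zero events in n infants, the exact one-sided 95% upper limit is 1 - 0.05^(1/n). For n = 166 it is 1.8%. For n = 133 it is 2.2%. Both ignore twin clustering. Without recording, no such limit can be stated.

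**The case against.** The strongest reply is that the restriction is deliberate. Most infants will have serious events with or without the trial, so section 8.1.4 drops blanket recording, and section 8.1.3 makes the modality subject to agreement with the authorities. That justifies not recording all adverse events. It does not address events attributable to a research procedure, which the causality scale in Table 3 could sort just as it sorts those of the oximeter.

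Several stronger readings are tempting, and the protocol does not support them:
- **That all these procedures are imposed on every infant.** Only the EEG is written that way. Blood comes from an existing catheter, so the protocol asks for no new puncture. The MRI is separately consented, and needles are optional.
- **That nothing but oximeter and guideline harm is recorded.** Deaths and the listed morbidities are recorded whatever their cause.
- **That the group comparison is distorted.** Table 2 schedules the same procedures in both arms, so no treatment estimate is biased by this.
- **That the ultrasounds belong in the count.** Section 1.4.1 calls ultrasound a standard tool, so the six scans are left out here.
- **That a number of missed events can be projected.** The protocol gives no reaction rate for any of these procedures.

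Two further limits stand. The consent pages are not available, so what parents are told about procedure risk cannot be judged. The safety committee's charter is a separate document and may say more than section 8.3.

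**Conclusion.** The gap is real but bounded. As written, the protocol has no category, and for the MRI no time point, for a non-fatal harm caused by the EEG electrodes, the research blood sampling or the MRI, unless it is a listed morbidity. Such an event would be neither recorded nor attributed, and it has no defined route to the sponsor or the safety committee. The exposure is at most 664 procedures. How many harms would be missed is unknown.

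The conclusion rests on the definitions in 8.1.1, Table 4 and the remit in 8.3 being applied as written. It does not depend on any assumed event rate. It concerns patient safety and completeness of harm reporting; the primary analysis and the power are untouched. A related inconsistency needs resolving at the same time: Table 1 ends recording of serious reactions at 72 hours, while Table 2 marks them at 7 days.

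**What to change.** 1. In 8.1.1, extend the definitions of adverse reaction and serious adverse reaction to responses related to procedures performed for the trial (EEG, research blood sampling, MRI), in both arms. Keep the threshold of a certain or probable/likely relation already used in Table 4.
2. Align the safety committee's remit in 8.3 with the wider definition.
3. Add a recording point at the MRI in Tables 1 and 2.
4. Send serious procedure-related events by the 24-hour route in 8.1.5.
5. Reconcile the 72-hour and 7-day windows for serious reactions in Tables 1 and 2.

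The cost is some additional event reports, one or two fields in the electronic case record form, and a protocol amendment. Under section 6.6 the amendment needs agreement from the sponsor, ethics committees and authorities, and section 4.5 expects 12 countries, so it is more than a wording change. No new procedure on any infant is needed.
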